## Abstract

**Introduction:**

Obesity has reached epidemic proportions globally, posing significant challenges to public health and economic stability. In China, the prevalence of obesity is increasing rapidly, particularly among pregnant women, who face unique risks due to the complex interplay between obesity and pregnancy outcomes. This study aims to evaluate the effectiveness of an Artificial Intelligence-driven Therapeutic Lifestyle Change (AI-TLC) intervention in improving health behaviors and outcomes among obese pregnant women in China.

**Methods and analysis:**

This randomized controlled trial will recruit pregnant women aged 18 years or older with a singleton pregnancy between 8 and 12 weeks of gestation and a pre-pregnancy BMI of ≥30.0 kg/m^2^. Participants will be randomly assigned to one of three groups: a manual intervention group, an AI intervention group, and a combined AI and manual intervention group. The intervention will focus on therapeutic lifestyle changes, including behavioral modifications, dietary adjustments, and physical activity promotion, supported by a multidisciplinary team. Primary outcomes will include maternal BMI, weight, and adverse pregnancy outcomes, while secondary outcomes will assess physiological indicators, quality of life, mental health, and lifestyle factors.

**Results:**

The study will evaluate the effects of health interventions on obese pregnant women through primary outcomes (e.g., BMI, weight, adverse pregnancy outcomes) and secondary outcomes (e.g., physiological indicators, quality of life, mental health) using various statistical methods. The results will provide insights into the intervention's effectiveness and cost-effectiveness across different socioeconomic groups.

**Discussion:**

The anticipated findings are expected to demonstrate the efficacy of AI-TLC interventions in managing obesity during pregnancy. This study will contribute valuable evidence to the limited research on AI-based interventions for obese pregnant women, offering potential implications for the development of personalized, efficient, and innovative health strategies. The findings may also inform public health initiatives aimed at improving maternal and child health outcomes in the context of obesity.

## 1 Introduction

Obesity is an abnormal or excessive fat accumulation that can impair health. A research study shows that the total number of obese children, adolescents and adults worldwide by 2022 has exceeded 1 billion, of which 879 million are adults. Since 1990, obesity rates among adults have more than doubled among women (1). In China, the problem of overweight and obesity among residents is increasingly prominent, and the rate of overweight and obesity among all age groups in urban and rural residents continues to rise, and more than half of adult residents are overweight or obese. Obesity is not only an independent health problem, but also an important risk factor for multiple chronic diseases such as type 2 diabetes, cardiovascular disease, hypertension, and so on (1, 2). Obesity often coexists with other chronic diseases, creating a complex network that complicates treatment and management. Furthermore, obesity is linked to several biological mechanisms, such as inflammation, oxidative stress, and endocrine disorders, which may collectively contribute to the development of chronic diseases (3). With the increasing rate of obesity worldwide, the incidence of chronic diseases increases, placing a substantial burden on individual health, healthcare systems and socioeconomic (4).

Maternal obesity is associated with a range of adverse pregnancy outcomes, including gestational diabetes mellitus, gestational hypertension, preeclampsia, need for cesarean delivery, and large for gestational age (5–8). These complications not only affect the health of the mother during pregnancy but may also have long-term consequences for the child, such as increased risk of prematurity, large for gestational age, birth-related trauma, hypoglycaemia, neonatal intensive care unit admission, stillbirth, increased risk of obesity and metabolic disorders in later life (8–11).

According to the study, obese patients had 46% more hospitalization, 27% more clinic and outpatient costs and 80% more prescription drugs compared with normal weight individuals (12). In recent years, several guidelines and expert consensus on obesity and chronic diseases have been published at home and abroad, but most of them are suggestions for evaluation methods or diagnosis and treatment procedures, and lack systematic prevention and management countermeasures. Therefore, it is important to study effective strategies for chronic obesity intervention to improve public health.

To address this challenge, comprehensive interventions are needed. At present, foreign interventions for obesity include lifestyle intervention, weight loss drugs and bariatric surgery. Lifestyle changes are fundamental to obesity management, including healthy eating, regular exercise, and psychological support. Most guidelines for health professionals managing patients with obesity recommend integrated lifestyle planning as a first step (13). Other scholars found that within 12 months, lifestyle and behavioral intervention alone resulted in an average weight reduction of intervention group members, and a 46% remission rate of type 2 diabetes (14). Maintaining weight loss is challenging long term through life changes for most people, so clinical practice guidelines recommend multiple ways of treatment, including taking weight loss drugs or performing bariatric surgery. Regulators around the world have approved several weight-loss drugs for long-term weight management: orlistat, phentermine, naltrexone-non-acetone (15). In addition, Martin Bossart and others showed that a combination of glucagon-like peptide-1 (GLP-1), glucose-dependent insulin polypeptide (GIP) and glucagon (GCG) active tripeptide enzyme (SAR441255) to improve weight loss and blood glucose control, while buffer the risk of long-term GCG receptor agonists, the greatest potential in weight loss drugs (1). Common bariatric surgery includes laparoscopic sleeve gastrectomy, gastric bypass bariatric surgery and anastomotic gastric bypass surgery.

In China, traditional Chinese medicine is early on obesity, and has unique advantages in comprehensively improving the symptoms of obese patients, regulating the blood lipid level in the body, and improving the waist and hip circumference of obesity (16).

Drugs and surgery are undoubtedly the quickest options, but their safety profile has yet to be considered. Carolina et al. pointed out that the weight loss response of weight loss drugs varies widely among individuals and their adverse effects are different, such as liststa and Gl-1-1 receptor agonists mainly have adverse effects on the gastrointestinal tract (17). The most common surgical treatment is laparoscopic sleeve gastrectomy as well as gastric bypass bariatric, with long-term results and strong evidence of safety (18). But both procedures still cause complications such as gallstone and malnutrition (15). In this way, lifestyle interventions have their unique advantages in terms of safety and convenience.

Therapeutic Lifestyle Change (TLC) is an intervention to treat and prevent chronic diseases by improving lifestyle. It includes measures such as dietary modification, increased physical activity, smoking cessation, and weight loss, designed to reduce risk factors for disease and improve patients' overall health. The effect of therapeutic lifestyle interventions has been demonstrated in several studies. For example, meta-analysis of RCTs and non-RCTs showed that lifestyle interventions had a borderline effect on restricting gestational weight gain (19). Another study found that TLC interventions could improve criteria for metabolic syndrome and further regulate in combined with medication (such as amlodipine/atorvastatin) (20). However, at present, this technology has hardly been applied to patients with co-patients of obese chronic diseases. Therefore, we would adopt therapeutic lifestyle intervention for co-patients with obese chronic diseases, and study the effect of the intervention and the adaptation of people of all ages.

Although previous studies proved that antenatal dietary and lifestyle intervention in obese pregnant women reduces maternal pregnancy weight gain, how to implement the lifestyle intervention in the most effective and low labor cost way still need to be studied (21). In recent years, AI intervention has attracted attention as a new intervention, and AI-based intervention research is being rapidly developed in China. For example, studies explored the current state of development, protocol guidelines, reporting norms, and challenges facing clinical trials of AI-based interventions (22). Internationally, the research of AI intervention has also made significant progress. For example, a study published in Nature-Medicine explored how AI guidance can help with the early detection of heart disease in routine practice. This study indicated the positive results of low ejection fraction screening through the electronic medical records, and found that the AI intervention overall improved the diagnostic rate of low ejection fraction by 32% (23). This indicates the great potential of the application of AI intervention in the field of medical diagnosis. Despite the remarkable results of AI interventions in some areas, some challenges exist. For example, the development of the CONSORT-AI extension and SPIRIT-AI extension guidelines suggests that interventions involving AI need to be rigorously evaluated prospectively to clarify its health impact (24, 25). Therefore, the development of higher quality AI applications and evaluate their potential to improve the condition of obese chronic disease patients remains an important area that we need to study.

In China, patients with obesity and chronic diseases face severe challenges. Internationally, interventions for patients with obesity and chronic diseases are often supported by professional medical teams and community health programs. In contrast, Chinese patients tend to rely on hospitals and themselves. In view of China, therapeutic lifestyle intervention combined with AI technology, as an innovative intervention, is easy to implement and cost-effective. Through AI technology, personalized lifestyle advice can be provided, monitoring patient health data and timely adjusting treatment options. This intervention not only facilitates patients to receive management at home, but also can deliver professional support to meet the needs of patients in the process of lifestyle change effectively and efficiently. Therefore, research targeting this area has important practical significance and urgency.

This study designed a randomized controlled study to propose an AI-driven therapeutic lifestyle change (AI-TLC) intervention. Through personalization, continuous tracking feedback, intelligent decision aid, evaluate the influence of AI-TLC intervention on health behavior and health outcomes of obese pregnant women, determine the applicability and universality of AI-TLC intervention, provide innovative, efficient, and personalized health intervention for obese pregnant women, and provide new perspectives and methods for related scientific research and clinical practice.

Specific objectives are:

Primary: Can the intervention program driven by artificial intelligence (AI)–facilitated therapeutic lifestyle changes effectively promote improvements in health behaviors and health outcomes among pregnant women who are overweight or obese?

Sub-question 1:

Do the effects of the intervention differ among pregnant women of varying ages and degrees of obesity?

Sub-question 2: From a cost-benefit perspective, which level of intervention is the most effective (human-only vs. AI-only vs. human + AI)?

Sub-question 3: What are the short-term, medium-term, and long-term effects of this intervention program? What mechanisms need to be added to achieve better long-term outcomes?

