### 2.2 Randomization

After recruitment, the research team will conduct a pre-enrollment assessment and post-enrollment informed consent with the participants and their families, followed by randomization grouping:

A comprehensive assessment will be conducted before the participants are enrolled, including structured questionnaires and clinical examinations.

The approved subjects were randomly divided into Manual intervention group, artificial intelligence intervention group (AI intervention group), artificial intelligence and artificial combined intervention group (AI & Manual intervention group). The specific randomization operation is as follows: This study uses a simple randomization method. Random number series were randomly generated by the study designer using the RANDBETWEEN formula in EXCEL. The project will divide the subjects into different groups according to the sequence, the intervention team will know the grouping results, and the subjects will not know the grouping results.

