The research design incorporates a single-blind experimental setup, wherein participants are unaware of their allocation status or the identity of the intervention provider.

The Manual intervention group receives personalized TLC plans developed by the multidisciplinary team based on individual health profiles. The AI intervention group follows plans generated by an artificial intelligence algorithm using the same health data. The Combined intervention group benefits from a hybrid approach, where AI-generated plans are supplemented with expert recommendations from the healthcare professional team.

This study's methodology aligns with the rigorous standards expected by academic journals, ensuring a controlled and systematic evaluation of the TLC intervention's impact on health behaviors and outcomes among obesity pregnant women (Figure 2).

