### 2.6 Statistical analysis

Participants' socio-demographics are presented as count and proportion, and the χ^2^ test was used to assess categorical variables. The continuous variables normally distributed were assessed by the student's *t*-test. The Fisher's exact or the chi-square test was adopted for categorical data, and statistical significance was set at *p* < 0.05. The main analysis was performed using generalized estimating equations (GEE) model. The GEE solved the problem of correlation of longitudinal data, utilizing the results of each measurement in the longitudinal data, which greatly reduces the loss of information (20). To clarify whether socioeconomic status affects the effectiveness of ILSM, we conducted several subgroup analyses for physiological health outcomes and health behaviors, and added the interaction terms to generalized estimating equations model to assess the interactions between time (at baseline, 3-month, 6-month, and 18-month) and group (intervention and control). We also used GEE to analyze the health benefits of intervention and control groups among participants with different socioeconomic status. Significance level of the associations in the final model was set at *P*-value 0.05. The data were analyzed using SPSS 20.0 (IBM Corporation, Armonk, NY, USA).

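### The primary objective asks whether AI-TLC is effective, but all three arms receive TLC, so it should be restated as a comparison with Manual TLC

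*Protocol article*

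**What the plan says.** - **Objective.** Under the specific objectives (section 1), the primary question is whether the AI-facilitated programme can "effectively promote improvements in health behaviors and health outcomes among pregnant women who are overweight or obese". The abstract has the same form: "This study aims to evaluate the effectiveness of an Artificial Intelligence-driven Therapeutic Lifestyle Change (AI-TLC) intervention". Its discussion paragraph expects efficacy of AI-TLC to be shown. None of these statements names a comparator.
- **Comparative question.** Comparison of the arms appears only as Sub-question 2, from a cost-benefit perspective: "which level of intervention is the most effective (human-only vs. AI-only vs. human + AI".
- **Arms.** The abstract lists "a manual intervention group, an AI intervention group, and a combined AI and manual intervention group", and section 2.2 randomises to the same three. Section 2.3 applies TLC to the whole study. For the manual arm, "The Manual intervention group receives personalized TLC plans developed by the multidisciplinary team based on individual health profiles". For the AI arm, "The AI intervention group follows plans generated by an artificial intelligence algorithm using the same health data". The combined arm has the AI plan with added recommendations from the professional team.
- **Analysis.** Section 2.6 makes GEE the main analysis, with a time-by-group interaction in which group has two levels, intervention and control. It adds: "We also used GEE to analyze the health benefits of intervention and control groups".
- **Sample size.** Section 2.1.1 gives an effect size of 0.5, two-sided alpha of 0.05, 90% power and 40 per arm. It does not say which contrast this serves.

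**The concern.** The objective asks about an absolute effect, whereas the randomisation supports relative effects only. Manual TLC is a personalised programme from a multidisciplinary team, so it is neither usual care nor an untreated control. No arm shows what would have happened without TLC.

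The two-group wording of section 2.6 hides this. It suggests a control that the design does not contain, and it leaves open which of the three arms is meant or whether arms are pooled.

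At stake is what may be concluded. If the arms turn out alike, the primary question as worded has no answer from the randomised comparison. The remaining route to a statement of effectiveness would be change from baseline within an arm. Assessments run from about 12 weeks of gestation to after delivery, and weight and BMI change over that period whatever is done.

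**Working it through.** **1. What the randomisation identifies.** Let M, A and C be the mean outcome under Manual, AI and combined delivery, and N the mean under no TLC. Three contrasts are randomised: A − M, C − M and C − A. The objective as worded concerns A − N (or C − N), and

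A − N = (A − M) + (M − N).

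The trial estimates the first term. No arm informs the second.

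- If A is better than M, A is also better than N provided Manual TLC is no worse than nothing. This is indirect support resting on an outside assumption.
- If A − M is near zero, then A − N is about M − N, which is unknown. All arms may work, or none.

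**2. Within-arm change.** Write the change in an arm as its treatment effect plus G, the change due to pregnancy itself. G cannot be separated from the effect within an arm. In the group-by-time term the difference between two arms is taken and a common G cancels. What remains is again a relative effect.

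**3. Objective, arms and analysis side by side.**

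| Place | Comparison implied |
|---|---|
| Primary objective and abstract | AI-TLC, no comparator |
| Sub-question 2 | human vs AI vs both |
| Sections 2.2 and 2.3 | three active TLC arms |
| Section 2.6 | intervention vs control |
| Section 3 (Discussion) | AI-TLC against manual delivery alone |

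Sub-question 2 and the Discussion fit the design. The primary objective and section 2.6 do not.

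**4. Consequence for the sample size if the objective becomes comparative.** Inputs from section 2.1.1: 0.5, two-sided 0.05, 90%, 40 per arm. Assumption: 0.5 is a standardised mean difference d, since its type is not stated.

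The plan's figure first: n = 2(z₀.₉₇₅ + z₀.₉₀)²/d² = 2(1.960 + 1.282)²/0.25 = 84.06, so 85 per arm (255 in total). The stated 40 is not reproduced. Other readings at 90% power do not give it either:

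- one-sided two-sample: 69
- three-group ANOVA with f = 0.5: 18
- three-group ANOVA with f = 0.25: 69
- one-sample: 42.03, rounded up to 43
- paired t: 44

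Forty would fit with assumptions the article does not state, for example:

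- ANCOVA with baseline correlation 0.72: 84.06 × (1 − 0.724²) = 40
- the mean of four follow-ups with correlation 0.30: 84.06 × (1 + 3 × 0.301)/4 = 40

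Power with 40 per arm is Φ(d√(n/2) − z) = Φ(2.236 − z), without such gains:

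| Alpha | z | Power | n per arm for 90% |
|---|---|---|---|
| 0.05 | 1.960 | 61% | 85 |
| 0.05/2 | 2.241 | 50% | 100 |
| 0.05/3 | 2.394 | 44% | 109 |

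The smallest d detectable with 90% power at alpha 0.05 is 3.242 × √(2/40) = 0.72.

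**The case against.** The introduction treats antenatal lifestyle intervention in obese women as already shown to reduce weight gain. It puts the open question as how to deliver it well with little labour. On that view Manual TLC is a proper active comparator, and the trial tests what AI adds. Sub-question 2 and the Discussion show the comparative intent, so the fault might be called loose wording in one sentence and the abstract.

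Much of this stands. It shows that the design suits a comparative question, and it is why the remedy is rewording and not a new arm. It does not rescue the objective as written, because the comparison of arms is placed in a sub-question on cost-benefit. Nor is the premise secure within the article, which elsewhere summarises the pooled evidence on gestational weight gain as borderline.

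Two stronger readings are tempting and should not be made:

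- **That the trial carries no information at all on effectiveness.** Superiority over Manual would be indirect evidence, as shown above.
- **That the sponsor plans to claim effectiveness from pre-post change.** No section says so. The time-by-group interaction in section 2.6 is a between-arm comparison. Pre-post inference is a risk that the wording leaves open, not a stated plan.

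The two-group wording could also belong to a wider mismatch, since section 2.6 lists time points (3, 6 and 18 months) that differ from the visits in section 2.1. That may explain its origin, but it still leaves the main analysis without a defined reference arm.

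**Conclusion.** The point holds. The primary objective and the abstract pose an absolute question of effectiveness. The three randomised contrasts are all between active TLC deliveries and give no direct randomised evidence against no TLC. A positive result against Manual would support effectiveness only if Manual TLC is assumed no worse than nothing, and a null result could not be interpreted on the question as worded. Section 2.6 names a control that the design does not define.

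This rests on the text of the abstract and sections 1, 2.2, 2.3 and 2.6. Figure 1 is not shown, but the text is consistent on three active arms. The power figure (about 61% per pairwise contrast) depends on 0.5 being a standardised difference, with no gain from baseline or repeated measures. Rewording the objective exposes that weakness but does not create it. The trial can still give useful comparative evidence.

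**What to change.** 1. Restate the primary objective and the abstract as a comparison of AI-based TLC delivery (AI, and AI+Manual) with Manual TLC, in line with Sub-question 2 and the Discussion.
2. In section 2.6, replace the two-group wording with the three randomised arms, Manual as reference, in the group-by-time GEE model.
3. State that within-arm change over gestation is descriptive and will not support a claim of effectiveness.
4. State for each primary contrast whether it is for superiority or non-inferiority, at which visit, and how two contrasts share alpha. The low-labour rationale could suit non-inferiority of AI alone, so this choice is the sponsor's. No primary visit is named at present.
5. Tie section 2.1.1 to the chosen contrast: what 0.5 measures, and any correlation assumed.

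Cost: the claim becomes narrower, and the stated 90% power may have to be lowered or justified. The rewording itself requires no added arm or patients. If the sponsor wished to keep 90% power at d = 0.5 without such gains, that would be a separate decision about size (85 per arm, or 100 with alpha split over two contrasts).
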